#### Additional exploratory outcome measures

These will be optional outcome measures for patients, which they can opt into via the consent form. These exploratory measures have been included to build on the insights gained from prior research.

##### Immune Markers {33}

Blood will be collected at baseline and at 6 weeks to assess markers of immune ageing and immune-mediated inflammation including (but not limited to) T-cell surface and intracellular phenotype analysis (with or without stimulation) and circulating biomarkers such as antibodies, cytokines, or other circulating proteins. A total of 50 ml (2 ½ tablespoons) venous blood samples will be taken from the arm by a trained member of the research team at the baseline and 6-week assessment visits. Blood samples will be divided into aliquots. Plasma, serum, and peripheral blood mononuclear cells will be separated. A whole blood sample will also be sent for FBC analysis via routine pathology laboratory analysis.

The samples will be stored at −80 °C (plasma and serum) or −150 °C (PBMCs) confidentially in a coded and anonymised form, in accordance with the Human Tissue Act 2004.

##### Heart Rate Variability

A noninvasive 12-lead ECG Holter device (Norav Medical) will be used. Data will be collected continuously for 24 h from patients in either group before and after the intervention period. In addition, resting 12-lead ECG recordings will be collected for 10 min at baseline and again after the intervention. Biomarkers of interest include QT variability, signal averaging ECG (fragmented QRS complexes), temporal T-wave morphology variability, and T-wave alternans. This will provide a wide analysis of heart rates that are suitable for a detailed assessment of the autonomic function before and after rehabilitation programmes (Table 2).

**Table 2 Tab2:** Spirit Figure

	STUDY PERIOD		
	Enrolment	Intervention	Post-allocation
TIMEPOINT	0	0–6 weeks	6–8 weeks
**ENROLMENT:**			
Eligibility Screen	X		
Informed Consent	X		
Allocation	X		
**INTERVENTIONS:**			
Rehabilitation		X	
Control		X	
**ASSESSMENTS:**			
Incremental Shuttle Walking Test (ISWT)	X		X
Short Physical Performance Battery (SPPB)	X		X
Quadriceps Strength	X		X
Physical Activity Monitoring	X		X
Endurance Shuttle Walking Test (ESWT)	X		X
EuroQol 5-Dimension 5-Level (EQ-5D-5L)	X		X
Covid-19 Yorkshire Rehabilitation Scale (C19-YRS)	X		X
Patient Health Questionnaire-9 (PHQ-9)	X		X
Generalised Anxiety Disorder-7 (GAD-7)	X		X
Medical Research Council (MRC) Dyspnoea Scale	X		X
Functional Assessment of Chronic Illness Therapy – Fatigue (FACIT-F)	X		X
Montreal Cognitive Assessment (MOCA)	X		X
DePaul Symptom Questionnaire – Short Form (DSQ-SF)	X		X
**OPTIONAL EXPLORATORY MEASURES:**			
Immune Markers	X		X
Heart Rate Variability	X		X

### Uptake, compliance and completion

There will be a screening log recorded of the number of people approached, which will be used to compare with those who uptake and consent.

Quantitative measure of completion in the intervention group will be defined as the number of patients attending 75% of their scheduled sessions (75% selected to align with national rehabilitation guidance [44]) or attended follow-up assessment.

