### Face-to-face rehabilitation (intervention) {11a and 11c}

Individuals will complete an individualised symptom-titrated programme of exercise, education, and self-management for 6 weeks. The programme will comprise two supervised sessions per week delivered by healthcare professionals.

Six weeks have been purposefully selected as the intervention period to align with current clinical provision in Leicester. Aligning the intervention period with that used clinically will consolidate clinical expertise and support implementation.

The rehabilitation programme will consist of aerobic exercise (i.e. treadmill/ground walking at 80% of the incremental shuttle walk test (ISWT) speed where tolerated and lower-limb cycling on a static bike) and resistance exercise training (upper and lower limb strength exercises). The exercise intensity and duration will be tailored to the individual’s current abilities, assessed in their first visit.

In addition to the supervised sessions, patients will be asked to perform home-based exercise sessions which align with the supervised sessions to include the following: daily walking, three aerobic exercise sessions, and one resistance exercise session each week. Participants will be asked to record their progress in a self-reported diary, which will be used in conjunction with self-reported symptoms at the face-to-face sessions for the delivering clinicians to monitor symptoms and guide exercise modifications and progression.

Each rehabilitation session will include an educational discussion (approx. 30–60 min) delivered by a member of the multidisciplinary team. These discussions will be facilitated by information sheets saved from the Your COVID Recovery (YCR) website repository. Topics covered will include the following: getting moving again, managing activities of daily living, breathlessness, fatigue management, and recognising symptoms of worsening in response to exercise, fear and anxiety, mood and coping, memory and concentration, cough, eating well, sleep hygiene, goal setting, headaches, managing symptom exacerbation and fluctuations, and returning to work. At the end of each session, there will be an opportunity for discussion and question and answer.

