#### Phase 2 – one-to-one semi-structured interviews

Interviews will be conducted by the lead researcher with those that declined (elected not to participate in the intervention at all) and those that dropped out of the programme (commenced but did not complete the intervention) to explore why people did not attend/complete in order to develop an understanding of the barriers to attendance. The data gathered from these interviews will help to identify and explore any healthcare inequalities that may be evident and whether there are any differences in the demographics of those who choose not to attend/complete. These will take place either face to face or virtually (by telephone or video conference) depending on the participants’ preference. It is expected that the interviews will take between 45 and 60 min depending on the responses.

The acceptability framework will inform the topic guide [28]; however, the nature of semi-structured interviews offers the researcher agency to adapt the interview for each participant depending on the answers provided.

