#### Primary outcome

Maximal exercise capacity was measured by absolute change in ISWT distance (in metres) 6 weeks after baseline (±2 weeks). The ISWT will be performed in line with technical standards [32]. In brief, the test is an externally paced, incremental test that requires the patient to walk around a 10-m (m) course at a target speed dictated by audio bleeps. As a maximal, progressive test, the walking speed starts slowly but increases each minute, with the test terminated when the patient is no longer able to keep up with audio cues or by the assessor if the required speed is not attained. The test will be performed twice pre-intervention for familiarisation, with the highest distance achieved used for exercise prescription (ESWT speed). The test will be repeated once after the intervention (Table 1).

**Table 1 Tab1:** Secondary outcome measures

Acceptability	Physical Measures	Questionnaires
Quantitative measure of completion in the intervention group	Short physical performance battery (SPPB) [33]	Generic HRQoL: EQ-5D-5L [34]
Qualitative evidence via focus groups and semi-structured interviews	Physical activity monitoring: ActiGraph accelerometer device [35]	Fatigue: Functional Assessment of Chronic Illness Therapy Fatigue Scale (FACIT-Fatigue) [36]
	Maximum isometric quadriceps strength (kg) [37]	Depression: Patient Health Questionnaire (PHQ9) [38]
	Endurance Shuttle Walk Test (ESWT) (seconds) [39]	Anxiety: Generalised Anxiety Disorder 7-item scale (GAD7) [40]
		Breathlessness: MRC Dyspnoea scale [41]
		Covid-specific HRQoL: Modified C19-YRS [42]
		Cognitive Function: Montreal Cognitive Assessment (MoCA) [43]
		Post Exertional Malaise: DePaul Symptom Questionnaire Short Form (DSQ-SF) [25]

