### Statistical analysis {20a, 20b and 20c}

The analysis will compare the intervention group to the usual care group. Changes in the primary outcome (ISWT distance) will be compared between the groups using a paired *t*-test (or nonparametric equivalent if the data is not normally distributed). Two sensitivity analyses will be conducted for the primary outcome: (1) Missing data will be imputed using multiple imputation allowing for a full ITT analysis and (2) a per-protocol analysis with those that adhere to the intervention defined if they attended 75% of face-to-face sessions or attended for follow-up appointments.The ISWT will also be analysed using generalised linear mixed models (GLMM); this will allow for in-group adjustments for other variables which may add to the richness of the qualitative data at the point of data mixing.

Secondary outcomes are not powered. All analysis of the primary and secondary outcomes will be performed using R (Version 4.3.1), [48]. Continuous variables will be analysed using the *t*-test or nonparametric equivalent. Categorical variables will be analysed using the chi-squared test or non-parametric equivalent.

Blood biomarkers will be analysed using generalised linear mixed models (GLMM) or similar, with intervention group (control vs face to face), time point (pre vs post), and group × time treated as fixed effects; a random intercept will be included for the participant identifier, and all models will be adjusted for sex and baseline values for each variable.

For the heart rate variability, data will be analysed using robust signal processing approaches by a research associate. Advanced HRV analysis will be performed with the Holter ECGs. Biomarkers of interest include QT variability, signal averaging ECG (fragmented QRS complexes), temporal T-wave morphology variability, and T-wave alternans. These features will be compared and combined to be further correlated with patient-specific characteristics.

GLMMs will be fitted using the lmer function from the lme4 package [49]. Missing data for the primary and secondary outcomes will be imputed using a Bayesian framework. GLMMs will be fitted to outcomes with and without imputation. Imputation was performed using the JointAI library [50].

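### Completion and per-protocol adherence can both be met by attending follow-up alone, so the 75% attendance threshold excludes nobody with an observed outcome

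*Protocol article*

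**What the plan says.** The rule appears twice in the protocol article. Under Uptake, compliance and completion, the quantitative completion measure for the intervention group is the number of patients "attending 75% of their scheduled sessions (75% selected to align with national rehabilitation guidance [44]) or attended follow-up assessment". In the Statistical analysis section, the second sensitivity analysis of the primary outcome is "a per-protocol analysis with those that adhere to the intervention defined if they attended 75% of face-to-face sessions or attended for follow-up appointments". No section sets a minimum number of sessions for those who qualify through follow-up.

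Three other parts of the article bear on this:

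- **Outcome timing.** Under Primary outcome, the ISWT is done before the intervention and then "The test will be repeated once after the intervention". The schedule in Table 2 places this at the 6 to 8 week assessment.
- **Handling of missing data.** The first sensitivity analysis reads "Missing data will be imputed using multiple imputation allowing for a full ITT analysis". Because imputation is named there as a departure from the main comparison, the main comparison appears to use observed outcomes. The article does not say so directly.
- **Use of completion.** Table 1 lists completion in the intervention group as the quantitative acceptability measure. The Phase 2 interviews include "those that dropped out of the programme (commenced but did not complete the intervention"), and Phase 3 invites completers to focus groups.

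**The concern.** A per-protocol sensitivity analysis is meant to show whether the estimated effect changes when people who had little of the programme are set aside. That needs a rule which can set them aside. Here the second limb is satisfied by turning up for the visit at which the outcome is measured, so the attendance limb has no effect among people with data. Agreement between the primary and per-protocol results could then be taken as robustness to non-adherence when the definition alone had produced it.

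The completion measure has the same weakness. The first secondary objective is acceptability judged by engagement, and the article ties the 75% figure to national rehabilitation guidance. A count that retention alone can satisfy does not measure engagement and cannot be compared with that benchmark.

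There is also a loose end in the qualitative work. Someone who stopped attending but came back for assessment completes under the quantitative definition, yet looks like a drop-out in the Phase 2 description. These people may have much to say about barriers to attendance.

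**Working it through.** The plan gives no completion or adherence figure to reproduce, so the check is on the logic of the rule, followed by an illustration.

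**Inputs from the protocol article**

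- Sessions: two per week for 6 weeks = 12. Reading the threshold as at least 75%, 0.75 × 12 = 9 sessions.
- Intervention arm: 56 recruited at 1:1, so 56 / 2 = 28.
- Attrition allowance: 20%, so about 0.8 × 28 = 22.4, taken as 22 at follow-up.

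**Set logic**

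Let A = attended at least 9 of 12 sessions, F = attended follow-up, and O = follow-up ISWT observed. The test is done only at follow-up, so O lies within F.

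- Adherent as written: A or F.
- Per-protocol set with observed outcomes: (A or F) and O = O. This is the observed-data primary set, whatever the attendance. A participant with 0 of 12 sessions and a follow-up ISWT stays in (a limiting case).
- Control arm: controls have no sessions, so follow-up is the only limb they can meet. Every control with an observed ISWT stays in too.
- Per-protocol set with imputed outcomes: A or F. This adds people with at least 9 sessions and no follow-up, so it need not equal the primary set. It leaves out only those who missed both limbs. Low attenders seen at follow-up remain adherent.
- Completion as written: the count of (A or F), which is never below the count of A. The excess is the number in F but not in A.

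**Illustration (attendance and follow-up numbers are assumed)**

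Take 28 in the arm and 22 at follow-up, all 22 with an ISWT. Completion as written lies between max(A, 22) and min(28, A + 22). The observed per-protocol set under a sessions-only rule lies between A + 22 − 28 and min(A, 22).

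| A: at least 9 of 12 | Completion by sessions | Completion as written | Per-protocol arm as written | Per-protocol arm, sessions only |
|---|---|---|---|---|
| 11 | 39% | 22 to 28 (79% to 100%) | 22 | 5 to 11 |
| 14 | 50% | 22 to 28 (79% to 100%) | 22 | 8 to 14 |
| 17 | 61% | 22 to 28 (79% to 100%) | 22 | 11 to 17 |
| 20 | 71% | 22 to 28 (79% to 100%) | 22 | 14 to 20 |

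The floor on reported completion is simply the follow-up rate: 20/28 = 71%, 22/28 = 79%, 25/28 = 89%.

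**The case against.** **The follow-up limb may be meant for controls.** A per-protocol population must cover both arms, and controls have no sessions to attend. This is a fair reading of what the authors may have wanted in the analysis section. The text does not say it. That section speaks of adherence to the intervention, and the completion definition is confined to the intervention group. If controls were intended, the wording still needs correcting.

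**The collapse is not unconditional.** A reader might infer that the per-protocol and primary sets coincide in all circumstances. The document does not support that. It never calls the primary analysis complete-case, it also plans Bayesian imputation for the primary and secondary outcomes, and it does not say which data the per-protocol analysis uses. This objection stands, so the identity holds for observed outcomes only.

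**Completion may not be inflated in practice.** It might also be inferred that reported completion will be too high. The rule only permits this: it happens if at least one person below 75% returns for assessment, and the article gives no attendance data.

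**Routing to interviews or focus groups is not stated.** One could infer that low attenders who return will be sent to the completers' focus groups. Neither phase refers to the quantitative definition, and the Phase 2 wording could equally capture them as drop-outs. What remains is an ambiguity.

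**The stakes are limited.** The trial calls itself exploratory, its secondary outcomes are not powered, and acceptability also has a qualitative measure. That is right, and it bears on how serious the point is.

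**Conclusion.** The rule is wrong as written. Among participants with an observed follow-up ISWT, the 75% threshold excludes nobody. If the per-protocol analysis uses observed outcomes, it repeats the observed-data primary analysis on the same people and carries no information about adherence. If it uses imputed outcomes, the sets may differ, but low attenders seen at follow-up are still treated as adherent.

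For completion, only the direction is certain: never below the 75% attendance figure, and above it whenever someone under 75% attends follow-up. The 79% against 39% to 71% in the illustration rests on assumed numbers and is not an estimate.

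The two sections also differ in wording, assessment in one and appointments in the other. If appointments include routine clinical follow-up, the per-protocol rule is looser still.

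This should be fixed, but it does not threaten the main result. It affects one of two named sensitivity analyses, the only quantitative acceptability outcome, and the clarity of the qualitative sampling. The randomised primary comparison and the imputed ITT analysis do not depend on the rule.

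**What to change.** - Define intervention-arm completion and per-protocol adherence as attending at least 75% of scheduled supervised sessions (9 of 12), with identical wording in both sections.
- Report attendance at the follow-up assessment separately, as retention.
- State a separate per-protocol criterion for controls, for example that the follow-up assessment was attended.
- State whether the per-protocol analysis uses observed or imputed outcomes.
- State that the same attendance definition separates drop-outs (Phase 2) from completers (Phase 3).

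Requiring 75% attendance *and* follow-up would also make the per-protocol analysis distinct, but it would keep retention mixed into the completion measure.

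The cost is a possibly lower completion figure, a smaller and so less precise per-protocol set, and a protocol amendment through the sponsor and ethics committee while recruitment is open. The change should be made before data lock and before attendance by participant is reviewed, so that the data cannot influence the choice of rule.

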### Sample size {14}

The sample size for the randomised controlled trial is calculated based on the primary outcome of ISWT distance, with a change of 50 m at 90% power, a standard deviation of 17 m, and 0.05 type 1 error. These figures have been previously determined and referenced in the literature as the minimum important difference and variance for the ISWT [10, 45].

The sample size required is based on a power calculation for a two-sample *t*-test. The pwr.t.test function from the pwr package [46], in R, was used to calculate a required sample size of 23 participants per group, 46 participants in total. This has been inflated by 20% to allow for attrition, and, therefore, 56 participants will be recruited.

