**Methods:**

This mixed-methods study comprises a single-centre, randomised controlled trial to determine whether face-to-face rehabilitation increases exercise capacity compared to usual care alone in non-hospitalised patients with Long Covid, with embedded qualitative components to explore intervention acceptability in the context of healthcare inequalities. Usual care is as defined by the National Institute for Clinical Excellence (NICE) Covid-19 guidance.

The rehabilitation intervention will take place twice a week for 6 weeks and will combine symptom-titrated exercise with self-management education. The proposed sample size of 56 for the randomised controlled trial is calculated on the primary outcome of Incremental Shuttle Walking Test (ISWT) distance, with a change of 50metres (m) at 90% power, a standard deviation of 17 m, and a 0.05 type 1 error.

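### The stated sample-size inputs give 4 participants per group, not 23, so the difference, SD, power and n cannot all be right

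*Protocol article*

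**What the plan says.** The Sample size section specifies the calculation fully apart from sidedness. The outcome is ISWT distance, "with a change of 50 m at 90% power, a standard deviation of 17 m, and 0.05 type 1 error". On method it says "The sample size required is based on a power calculation for a two-sample" t-test, run with the pwr.t.test function in R. That function "was used to calculate a required sample size of 23 participants per group, 46 participants in total". The section then adds: "This has been inflated by 20% to allow for attrition, and, therefore, 56 participants will be recruited". It presents the difference and the spread as published values for the ISWT, citing two references.

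The Abstract (Methods) gives the same 50 m difference, "at 90% power, a standard deviation of 17 m, and a 0.05 type 1 error", with the total of 56. No other SD or target difference for the ISWT appears in the article. The Randomisation section gives 1:1 allocation.

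**The concern.** A 50 m difference against an SD of 17 m is almost three standard deviations. An effect of that size needs only a handful of participants, so a requirement of 23 per group looks wrong on sight.

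The calculation is the article's only quantitative justification for the trial's size, and it supports an explicit power claim for a comparative primary objective. If the inputs shown are not those used, a reader cannot tell what effect the trial was designed to detect or how variable the outcome was assumed to be. A reader who accepts 17 m as the SD would also take a null result as near-conclusive evidence against a 50 m effect. That reading may not be warranted.

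**Working it through.** **Inputs (Sample size section).** Difference 50 m; SD 17 m; power 90%; type 1 error 0.05; two-sample t-test; 1:1 allocation (Randomisation section). Sidedness is not stated. Two-sided is assumed, as it is the pwr.t.test default, and one-sided was also tried.

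**Formula.** With n per group, d = difference / SD, degrees of freedom 2n − 2 and noncentrality d × √(n/2), power is the probability that a noncentral t variable falls outside the two-sided 5% critical values. This is the calculation that pwr.t.test performs.

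**Attempt to reproduce 23 per group.**

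- d = 50 / 17 = 2.94.
- n = 3: power 76.7%.
- n = 4: power 93.0%.
- Exact solution for 90%: n = 3.71, so 4 per group (8 in total).
- n = 23: noncentrality 2.94 × √11.5 ≈ 9.97, power above 99.99%.

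The stated figure is not reproduced; 23 / 4 is a factor of about 6.

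**Variants tried.**

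| Change to the stated inputs | n required (per group; pairs for the paired test) |
|---|---|
| One-sided test | 3 |
| Paired t-test | 4 |
| SD of change taken as 17 × √2 | 7 |
| Type 1 error 0.01 | 6 |
| Type 1 error 0.001 | 8 |
| Power 99% | 6 |
| Difference and SD swapped (17 m, SD 50 m) | 183 |

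None gives 23.

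**What 23 per group implies.** Solving for d at 90% power, two-sided, gives d = 1.0005 at n = 22 and d = 0.977 at n = 23. A requirement that rounds up to 23 therefore has d between about 0.98 and 1.00. At d = 1 exactly, n = 22.02, so 23.

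- Keeping 50 m: SD = 50 / 1.0005 = 50.0 m to 50 / 0.977 = 51.2 m.
- Keeping SD 17 m: difference = 17 × 0.977 = 16.6 m to 17 × 1.0005 = 17.0 m.

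If the test were one-sided, the implied SD for 50 m would be about 56 to 57 m instead.

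**Power for 50 m with 23 per group.** The SDs below are assumptions, since the document gives only 17 m.

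| Assumed SD | Power |
|---|---|
| 50 m | 91% |
| 60 m | 79% |
| 70 m | 66% |
| 80 m | 55% |
| 100 m | 38% |

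**Attrition.** 46 × 1.2 = 55.2, so 56, which reproduces the stated total. The loss that still leaves 46 is 10 / 56 = 17.9%. Leaving 46 after a full 20% loss would take 46 / 0.8 = 57.5, so 58. With 22 per group, power is 88.6% to 90.0% at the implied SD of 50 to 51 m.

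**The case against.** The best defence is that the stated inputs, taken at face value, make the trial far larger than it needs to be, so the mismatch does no harm. The first half is true: nothing here shows under-powering. A reader might infer it from the power table, but those SDs are assumed and the document offers no basis for any of them. The defence does not rescue the 90% figure, which is still wrong for the inputs given.

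A reader might also infer that the SD is the faulty input and should have been about 50 m. The document does not support that choice: a 17 m difference with a 17 m SD gives 23 per group just as well. Whether 17 m is an SD, a standard error or the effect entered depends on cited sources that are not reproduced.

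Two side issues should not be pressed. The section refers to the spread as a variance, but both places call 17 m a standard deviation, in metres, so this is loose wording rather than separate evidence of error. The attrition step does what it says: adding 20% to 46 gives 56. The article does not promise 46 completers after a 20% loss, and the gap is two participants.

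Finally, the trial is described as exploratory. That lowers the stakes somewhat, but the article still states a comparative primary objective and claims 90% power for it.

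**Conclusion.** Wrong as written. The stated inputs require 4 per group, not 23, and at 23 per group they give power above 99.99%, not 90%. The difference, SD, power and n are mutually inconsistent, and no standard variant tried reconciles them. The conclusion needs only the stated inputs; two-sidedness is assumed, but a one-sided test moves the requirement further from 23.

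The 23 matches a standardised effect of about 0.98 to 1.00, and the document cannot show which input was different. What is established is that the 90% claim cannot be traced to its inputs. Actual power for 50 m depends on an SD that has yet to be sourced: if 50 m is the target and the true SD exceeds about 51 m, 46 evaluable participants fall short of 90% (two-sided).

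As a minor note, 56 recruited covers about 18% loss, with negligible effect on power.

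**What to change.** - Report the difference and SD actually entered into pwr.t.test, with the source of each, the sidedness, and whether the SD is for change in ISWT or for absolute distance. Do not choose an SD afterwards because it returns 23.
- Correct the Sample size section and the Abstract (Methods) to match.
- Restate the power for a 50 m difference with 46 evaluable participants at the sourced SD and over a plausible range around it. Replace the 90% claim if it is not met.
- Optionally, note that 56 allows for about 18% attrition.

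The cost is a recalculation and wording changes in two places. The downside is that the stated power may become less favourable. Whether 56 remains adequate should be left open until the inputs are known.
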